In our pilot work, Black and White patients with PD participated in a clinical phenotyping study, and the results showed no significant differences between the groups in sex, education, disease duration, Hoehn and Yahr stage, or Movement Disorder Society-Unified PD Rating Scale (MDS-UPDRS) part III Motor scores [10]. However, quantitative NIH Toolbox performance measures detected differences in gait and balance between Black and White participants with PD: gait speed (0.8±0.3 vs 1.1±0.2, *P*<.001), pegboard (41.4±15.6 vs 33.2±10.9, *P*=.04, and standing balance (32.7±13.1 vs 47±12, *P*<.01) [5]. In the nonmotor assessments, the Montreal Cognitive Assessment (23.4±3.1 vs 27±2.1, *P*<.005) and Symbol Digits Modalities Test (39.4±14.1 vs 49.6±9.1, *P*=.01) scores were worse in Black participants after correcting for education level. Hamilton Depression scale scores were worse in Black participants with PD compared with White participants (7±5.6 vs 4±3.5, *P*=.04), but other neuropsychiatric scales were similar between groups. The PD Quality of Life (PDQ-39) scores were higher (worse) in Black participants with worse ratings in participation in social roles and activities.

In summary, this pilot data showed differences in the motor examination, nonmotor features, and quality of life of Black patients with PD that warranted the current larger study. In our previous work and this protocol, race is self-identified by the patient as Black or White. Traditionally in the Chicago metropolitan area, this includes Black patients who are African, Afro-Caribbean, African American, or who report a mixture of races.

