### Study Setting and Design

The 7 study sites are Rush University, University of Maryland, University of Cincinnati, University of Pennsylvania, University of Chicago, Emory University, and Morehouse University (Figure 2). The sites were chosen based on US census data showing higher populations of Black persons in these geographic regions. A total of 400 Black patients with PD and 200 White patients with PD will be recruited. Patients who consent to enroll will have a single study visit encompassing data and sample collection for all 3 aims. A virtual option can also be used to complete questionnaires, followed by an in-person visit for the remaining measures.

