### Sample Size

The sample size was calculated for each primary outcome measure described above with 80% power and a 2-sided test to detect a similar effect size observed from our pilot data (Table 4). Bonferroni correction was applied to control the overall significance level at .05. The minimal sample size for these analyses requires 365 Black and 183 White participants to complete this aim. The data observed in 3 studies guided the sample size calculation for PD clinical management (White vs non-White or Black: 78% vs 62% for measure 1 [4], 92% vs 80% for measure 2 [56], and 10% vs 0.4% for measure 3 [57]). The sample size was calculated using 90% power and a 2-sided test for each primary measure. Bonferroni correction was applied to control the overall significance level at .05. With a 1:2 ratio, the largest sample size required among all 3 measures is 173 White patients with PD and 346 Black patients with PD. For the genetic studies, our sample size will permit exploratory analyses, and all data will be contributed to GP2 for fully-powered meta-analysis.

**Table 4 table4:** Pilot data effect sizes for sample size calculation.

Primary measures	White patients with PD^a^ (n=25), mean (SD)	Black patients with PD (n=25), mean (SD)
4-meter walk computed score	1.1 (0.2)	0.8 (0.3)
Balance *t* test score	47 (12)	32.7 (13.1)
Pegboard dominant score	33.2 (10.9)	41.4 (15.6)
MoCA^b^	27 (2)	23.3 (3.1)
SDMT^c^	49.6 (9.1)	39.4 (14.1)
PDQ-39^d^	12.8 (7.9)	22.5 (12.3)

^a^PD: Parkinson disease.

^b^MoCA: Montreal Cognitive Assessment.

^c^SDMT: Symbol Digit Modalities Test.

^d^PDQ-39: Parkinson’s Disease Questionnaire.

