### Statistical Analysis

Each primary outcome measure will be compared between Black and White patients with PD. Bonferroni correction will be applied. The primary outcome measures are a 4-meter walk computed score, Balance test *t* score, Pegboard dominant *t* score, MDS-UPDRS motor score [26], MoCA [33], SDMT [58], PROMIS Profile-29 Physical Function, and PDQ-8 [46]. For significant measures, linear regression analysis will be performed to examine further the difference between the 2 groups with adjustment for age, sex, and disease duration. The interaction effects of race with these 3 variables will be explored. Regression analysis for cognitive measures will adjust for depression and anxiety scales in addition to these demographics. Regression will also be adjusted for comorbidities using the Cumulative Illness Rating Scale-Geriatrics score. The study site effect will be controlled as a random effect in the model. All analyses will be done using SAS (version 9.4).

For the PD management analysis, each primary outcome measure will be compared between Black PD and White PD groups using the chi-square test or Fisher exact test. Bonferroni correction will be applied. A hierarchical logistic regression analysis will assess the determinants of racial disparities in management. Besides race, age, sex, and education, income, symptom severity, and comorbidities will be included in the model. The interaction effect of race with those variables will be explored. The study site effect will be controlled as a random effect in the model. Secondary analyses will investigate differences between White PD and Black PD groups in other clinical management measures, including telehealth, participation in clinical trials, and rehabilitation therapy.

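### The Aim 1 regression, fitted in the ordinary way, assumes one residual variance for both races; on the pilot SDs its confidence intervals would be about 12-15% too wide for five of six measures

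*Protocol article*

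**What the plan says.** Under Statistical Analysis, each primary measure is first compared between the races with Bonferroni correction; the test is not named. For measures that prove significant, "linear regression analysis will be performed to examine further the difference between the 2 groups with adjustment for age, sex, and disease duration". Comorbidity is added to the adjustment, as are depression and anxiety for the cognitive measures. Site enters as a random effect, and race interactions are explored. No residual variance structure or standard-error method is given.

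Under Study Setting and Design, "A total of 400 Black patients with PD and 200 White patients with PD will be recruited".

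Under Sample Size, Aim 1 is planned "with 80% power and a 2-sided test to detect a similar effect size observed from our pilot data (Table 4"), and "Bonferroni correction was applied to control the overall significance level at .05". The result is: "The minimal sample size for these analyses requires 365 Black and 183 White participants to complete this aim". Table 4 gives pilot means and SDs for six measures, 25 patients per group. The Background repeats several of these with the Black group first, for example "Symbol Digits Modalities Test (39.4±14.1 vs 49.6±9.1".

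**The concern.** An ordinary linear model, with or without a random site intercept, estimates one residual variance from everyone. When one group is both larger and more variable, that common estimate is pulled towards its variance. It is then applied to the smaller, less variable group, whose mean contributes much of the uncertainty in the difference. The standard error of the race difference comes out too large.

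The study's own planning table points to this configuration: two Black participants for each White participant, and a larger Black SD on every measure listed. At stake is the precision reported for the adjusted race differences, which are a main Aim 1 result. The race interactions come from the same model.

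**Working it through.** **Inputs.** Group sizes 200 White and 400 Black (Study Setting and Design). SDs from Table 4. Overall alpha .05 with Bonferroni (Sample Size). The divisor is not stated; I assume 8, the number of measures listed under Statistical Analysis, so alpha = .05/8 = .00625 and the two-sided critical value is 2.734.

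**The plan's own figure.** The requirement of 183 White and 365 Black does not reproduce from Table 4. Pegboard has the smallest standardized difference there. With unequal variances and 1:2 allocation it needs n(White) = (10.9² + 15.6²/2) × (2.734 + 0.842)² / 8.2² ≈ 46. Over divisors from 5 to 12 and other ways of pooling the SD, the largest requirement is 42 to 62 White participants. At 80% power, 183 White participants correspond to a standardized difference of sqrt(1.5 × (2.734 + 0.842)² / 183) = 0.32 (0.31 to 0.34 over those divisors). A measure missing from Table 4 may drive the figure: the MDS-UPDRS motor score and PROMIS Physical Function are primary but have no SDs there. I use the figure only as a sign that some measure may sit near 80% power.

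**Standard errors.**
- Common variance: SE = sqrt(sp² × (1/200 + 1/400)), with sp² = (199 × sW² + 399 × sB²)/598.
- Correct: SE = sqrt(sW²/200 + sB²/400).

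For MoCA, sp² = (199 × 4 + 399 × 9.61)/598 = 7.743, so the common-variance SE is sqrt(7.743 × 0.0075) = 0.2410. The correct SE is sqrt(0.0200 + 0.0240) = 0.2098. The ratio is 1.149.

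| Measure | SD White | SD Black | SD ratio | SE ratio |
|---|---|---|---|---|
| 4-meter walk | 0.2 | 0.3 | 1.50 | 1.138 |
| Balance | 12 | 13.1 | 1.09 | 1.030 |
| Pegboard | 10.9 | 15.6 | 1.43 | 1.122 |
| MoCA | 2 | 3.1 | 1.55 | 1.149 |
| SDMT | 9.1 | 14.1 | 1.55 | 1.148 |
| PDQ-39 | 7.9 | 12.3 | 1.56 | 1.150 |

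At 183 and 365 the ratios are practically the same (1.137 for the walk). For the five measures other than balance, a nominal 95% interval would cover about 97.2-97.6%, and a test at .00625 would have true size of about .002.

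**Does covariate adjustment remove it?** Not by itself. In 1,500 simulated data sets of 200 and 400 with SD ratio 1.5 and three covariates (unrelated to race, no site effect), the ordinary SE averaged 0.1176 against an empirical 0.1030, a ratio of 1.14. A heteroscedasticity-robust (HC3) SE averaged 0.1040.

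**Power at the Table 4 effects.** For pegboard, the weakest, the correct SE is 1.097 and the common-variance SE is 1.231. Power with the common variance is Φ((8.2 − 2.734 × 1.231)/1.097) = 0.999995. With the correct SE it is 0.999999. The other five are about 1.000 either way.

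**Power near the limit.** For an effect that the correct SE would detect with 80% power at .00625, a pooled test has power Φ(2.734 + 0.842 − 2.734 × SE ratio). That is 69.4% at an SE ratio of 1.122 and 66.7% at 1.150, a loss of 11 to 13 points.

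**Uncertainty in the SD ratio.** With 25 per group and normal data, the 95% interval for an observed ratio of 1.5 runs from 1.5/sqrt(2.27) = 1.00 to 1.5 × sqrt(2.27) = 2.26. The matching SE excess is about 0% to 26%.

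**The case against.** The strongest objection is that nothing here is stated wrongly. The article names a model, not a variance structure, and such detail usually belongs in an analysis plan, which is not shown. That stands as far as it goes: the article does not commit to a homoscedastic fit. But a default fit of the named model would carry the problem, and the article's own table gives reason to specify otherwise.

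The pilot evidence is also thin. The SDs are marginal rather than residual. The walk SDs are rounded so coarsely that the ratio could lie anywhere from 0.25/0.25 = 1.0 to 0.35/0.15 = 2.3. Table 4 lists PDQ-39 and a pegboard score, whereas the analysis uses PDQ-8 and a pegboard t score. Two primary measures have no SDs. All of this stands and limits how firmly the size can be stated.

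Two stronger readings are tempting. A reader might infer that the study gives away power. The documents do not support that: the regression runs only for measures already significant, so it cannot cause one to be missed at the first comparison; the test used there is not named; and power at the planned effects is about 100% with either SE. A reader might also equate the inflation with discarding 600 × (1 − 1/1.122²) ≈ 124 to 600 × (1 − 1/1.150²) ≈ 146 participants. That describes interval width only. A pooled standard error makes the test conservative but does not make the estimate itself more variable.

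**Conclusion.** The concern holds as a matter of precision. If the pilot SDs carry over to the residuals, and the regression is fitted with one residual variance, the intervals for the adjusted race difference are too wide by about 12-15% for the walk, pegboard, MoCA, SDMT and PDQ, and by 3% for balance. The direction is conservative and creates no false positives.

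A loss of power of up to about 13 points is conditional on three things: the unadjusted comparison pools the variance, the measure sits near 80% power, and its SD ratio resembles those in Table 4. The 365/183 requirement suggests that such a measure may exist, and the Background reports no significant pilot difference in the MDS-UPDRS motor score, which is primary. Without SDs for it, this cannot be taken further. Severity is low to moderate: a cheap improvement to a stated method, not an error that threatens the conclusions.

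**What to change.** Specify before analysis that the Aim 1 regressions use race-specific residual variances, for example PROC MIXED with REPEATED / GROUP=race and Satterthwaite degrees of freedom, or robust standard errors. Name the Welch test for the unadjusted comparison. SAS 9.4, already planned, supports this. The cost is one sentence in the plan and one line of code, with negligible loss of precision if the variances prove equal. No change to recruitment or data collection is needed.

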**Health literacy**		
	Rapid Estimate of Adult Literacy in Medicine	Health literacy [53]
	eHealth Literacy Scale	eHealth literacy [54]

^a^Minimum dataset.

^b^DBS: deep brain stimulation.

^c^FUS: focused ultrasound.

Participants who used a LAR for consent can complete assessments with assistance from a research assistant or proxy (care partner). All scales and questionnaires include a check box to document proxy assistance. The scales are administered by the neurologist (site investigator), study coordinator, or other staff as appropriate. The investigator completes the following assessments: MDS-UPDRS [26], Hoehn and Yahr Staging [27], Schwab and England Activities of Daily Living Scale [55], and the Cumulative Illness Rating Scale [51]. The investigator will also complete a questionnaire for the GP2 study that includes demographic and disease-specific information, such as disease duration. The study coordinator administers the rest of the study assessments.

Participants have blood samples drawn and sent to the National Institutes of Health for genetic studies. All participants are also offered enrollment into the Parkinson’s Foundation PD GENEration study in which seven PD genes are examined and results are disclosed to the participant. If the participant consents, an additional blood sample is shipped to the PD GENEration sequencing vendor (Fulgent Genetics). For these participants, genetic counseling, including results disclosure, is performed by either a PD GENEration genetic counselor from Indiana University or the genetic counselor at the Rush University site (either live or through telemedicine).

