### Outcome Measures

The primary outcome measures to characterize PD phenotypes include the NIH Toolbox Motor assessments (2-minute walk, 4-meter walk, balance test, pegboard test, and grip strength) [28]; the Montreal Cognitive Assessment (MoCA), Symbol Digit Modalities Test (SDMT), PROMIS Profile-29 Physical Function, Parkinson’s Disease Questionnaire-8 (PDQ-8), and the MDS-UPDRS. The primary outcome measures to assess PD clinical management include the proportion of participants with antiparkinsonian medications prescribed at the initial visit to the neurologist, the proportion of participants with initial treatment of depression, and the proportion of participants with PD surgical interventions. To characterize genetic risk variants in our sample, the frequencies of the 90 established common PD genetic risk variants based on published genome-wide association studies in a predominantly White population will initially be examined. The study team will also aggregate and summarize sequencing results from PD GENEration, including potential rare variants among 7 established PD genes. The proportion of LRRK2- and GBA-PD will be summarized based on either PD GENEration, which permits comprehensive detection of potential pathogenic alleles, or GP2 genotyping, which can detect many of the most common, recurrent pathogenic variants. Finally, exploratory genotype–phenotype analyses will determine whether established PD risk variants modify clinical manifestations in Black individuals.

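### The follow-up logistic model for PD management conditions on severity measured after the decisions it explains, cannot support race interactions for surgery, and should include disease duration for surgery

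*Protocol article*

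**What the plan says.** All places are in the protocol article.

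- **Primary comparison (Statistical Analysis):** "each primary outcome measure will be compared between Black PD and White PD groups using the chi-square test or Fisher exact test", with Bonferroni correction.
- **Follow-up model (same section):** "A hierarchical logistic regression analysis will assess the determinants of racial disparities in management". Its covariates: "Besides race, age, sex, and education, income, symptom severity, and comorbidities will be included in the model". Then: "The interaction effect of race with those variables will be explored". Site enters as a random effect. Disease duration is not listed, although the phenotype regression in the same section adjusts for it.
- **Outcomes (Outcome Measures):** the first is "the proportion of participants with antiparkinsonian medications prescribed at the initial visit to the neurologist". The others are the proportions with initial treatment of depression and with PD surgery.
- **Timing (Study Setting and Design):** "Patients who consent to enroll will have a single study visit". The Overview calls the design cross-sectional. No severity measurement at the time of a treatment decision is described.
- **Disease duration (Study Assessments and Outcome Measures, text after Table 3):** the investigator records "demographic and disease-specific information, such as disease duration".
- **Planning rates for surgery (Sample Size):** "10% vs 0.4% for measure 3", White versus non-White or Black.
- **Background (Introduction):** management disparities are described as probably associated with greater symptom severity. African Americans are reported as 5 to 8 times less likely to have deep brain stimulation.

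**The concern.** Three features of the follow-up model need attention.

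1. **Severity follows the outcome.** First prescribing, initial depression treatment and surgery all precede the study visit, whereas severity is measured at it. The article expects management to affect severity, and its first research question expects race to be associated with motor function and disability. On those premises, visit-day severity is a common consequence of race and past treatment. Conditioning on it can move the race odds ratio even with a perfect measurement and a large sample.
2. **Surgery is sparse.** Very few Black surgical cases are expected on the planning rate, yet the model has seven main effects, with up to six race interactions to be explored.
3. **Duration is absent.** Having had surgery accumulates with time since onset, so any racial difference in duration would pass into the race odds ratio for surgery.

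This model carries the explanatory claim about why management differs. A distorted or non-finite race estimate would be read as evidence on that question.

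**Working it through.** **Reproducing the plan's sample size.** Inputs from Sample Size: rates 78% vs 62%, 92% vs 80% and 10% vs 0.4%; two-sided alpha 0.05/3; power 90%; one White to two Black. With pooled variance and p̄ = (p_W + 2p_B)/3:

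n_W = [z(1−α/2)·√(1.5·p̄(1−p̄)) + z(0.90)·√(p_W(1−p_W) + p_B(1−p_B)/2)]² / (p_W − p_B)²

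Measure 2: p̄ = 0.84, and [2.394 × 0.4490 + 1.2816 × 0.3919]² / 0.12² = 172.7, so 173 White and 346 Black, as stated. Measures 1 and 3 need 167 and 95 White. The planning rates are therefore read as intended.

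**Events at 200 White and 400 Black.**

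| Outcome | Rarer category | Per slope, 7 main effects | Per slope, with 6 interactions (13) |
|---|---|---|---|
| First prescribing | 0.22×200 + 0.38×400 = 196 | 28 | 15 |
| Depression treatment | 0.08×200 + 0.20×400 = 96 | 14 | 7 |
| Surgery | 0.10×200 + 0.004×400 = 20 + 1.6 = 21.6 | 3.1 | 1.7 |

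Each covariate is counted as one slope and the site effect is left out.

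**Surgery at 0.4%.** P(no Black case) = 0.996^400 = 0.20. P(at most one) = 0.20 + 400 × 0.004 × 0.996^399 = 0.52. With no Black case the maximum-likelihood race odds ratio has no finite value. In 400 simulated data sets, with covariates unrelated to outcome and no site effect, separation (no finite estimate for at least one coefficient) occurred in about 23% with main effects and 69% with all interactions. At 173/346, expected Black events are 1.4, P(none) is 0.25, and the separation figures are 28% and 78%.

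**Surgery at the Introduction's ratio.** Reading the 5- to 8-fold figure as a ratio of proportions against 10% gives 10/8 = 1.25% to 10/5 = 2%, or 5 to 8 Black cases in 400. P(none) is 0.9875^400 = 0.007 or less. Separation on race itself is then unlikely. However, interacting race with all six covariates amounts to estimating six slopes separately within each race. The Black group would supply 5/6 = 0.8 to 8/6 = 1.3 events per slope, and at 0.4% only 1.6/6 = 0.3.

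**Effect of adjusting for later severity.** Assume severity (residual SD 1) = d·race + g·treatment + normal error, with race = 1 for Black. Then the severity-adjusted odds ratio equals the unadjusted one × exp(−g·d). The effects d and g are assumptions; the article gives neither.

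- Measure 1: OR = (0.62/0.38)/(0.78/0.22) = 0.46. For d = 0.5, g = −0.5 gives 0.46 × e^0.25 = 0.59, and g = +0.25 gives 0.46 × e^−0.125 = 0.41.
- Measure 2: OR = (0.80/0.20)/(0.92/0.08) = 0.35. The same settings give 0.45 and 0.31.
- If d = 0 or g = 0, nothing changes.

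Large simulations with d of 0.3 to 0.5 and g of −0.5 to +0.25 gave the same ranges. If Black participants are more severe and treatment lowers severity, adjustment understates the disparity.

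**Effect of omitting duration, surgery only.** With an assumed log-odds slope of 0.15 per year and a true odds ratio of 0.50, a Black-minus-White gap of −2 to +2 years moved the simulated estimate from about 0.39 to 0.67. Equal durations produced almost no change.

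**The case against.** A reader might infer that the race effects in the management aim are generally biased or not estimable. The documents do not support that. The primary comparisons are unadjusted chi-square or Fisher tests, which this model does not touch. Power for surgery at 200/400 is above 99% by the normal approximation, and Fisher's test copes with sparse cells. First prescribing and depression treatment have ample outcomes. Even for surgery at 0.4%, about 77% of simulated main-effects fits were finite, although a finite estimate resting on one or two Black cases is still unstable.

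Several further points have weight:

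- The 0.4% is a single planning rate. Participants come from movement disorder clinics, and the surgical questionnaire also covers focused ultrasound, so the realised rate may be higher. This weakens the claim about the main race effect but not the one about interactions.
- The article says interactions will be explored, not that all six enter together, so 13 slopes is the fullest reading. It names no estimation method, and an analysis plan could supply one.
- The term hierarchical may mean entry in blocks, which could yield a race effect without severity. The article does not say so.
- Severity at the time of a decision is a legitimate driver of treatment, and visit-day severity may be the only proxy. That justifies a sensitivity analysis, but not making it the only stated model.
- Bias from omitting duration requires a racial gap in duration. The pilot found no significant one, though with 25 per group. The later propensity matching might reduce a gap, but its variables are not given.
- Visit-day duration is not an evident confounder of the two initial decisions. Adding it there would repeat the timing problem.

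**Conclusion.** The point holds for the follow-up model only.

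1. **Severity:** the article states a model that conditions on a measurement taken after the outcome, and its own Introduction supplies the reason this matters. The direction and size of any distortion depend on assumptions. The illustrated range is 0.41 to 0.59 around 0.46, and it vanishes if treatment does not affect current severity or race has no direct path to it.
2. **Surgery:** race interactions are unsupportable whether 1.6 or 5 to 8 Black cases are expected. At 0.4%, the main race effect has no finite maximum-likelihood estimate in roughly 20% of samples. At the higher rates that risk is under 1%.
3. **Duration:** adding it to the surgery model is a free improvement rather than the correction of a demonstrated bias.

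The change is worth making because this model is the one meant to explain the disparities, and only 131 of 600 participants had been enrolled at submission.

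**What to change.** Revise the model paragraph for PD management in Statistical Analysis, or settle it in the analysis plan:

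- **All three outcomes:** make the model without current symptom severity the main one. Report the severity-adjusted model as a labelled sensitivity analysis, stating that severity was measured after the decision.
- **Surgery:** omit race interactions. Use Firth-penalised or exact logistic regression with a small covariate set: race, age and disease duration. Add education, income and comorbidities one at a time, so that the determinants question is still addressed. State how site is handled, as a fixed or stratifying term or left out, because ordinary Firth regression carries no random site effect.
- **First prescribing and initial depression treatment:** do not add visit-day duration. Exploratory race interactions can stay.
- **Primary chi-square and Fisher tests:** no change.

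No new data are needed, only wording and some analysis work. The price is no interaction results for surgery, slightly shrunken estimates, and simpler handling of site for that outcome.
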